### Sample size calculation

2.6

The smallest difference in HHS considered to be clinically important is 10 points. In our patient population, the average HHS is estimated to be 70 points, and the maximum standard deviation is estimated to be 20 points. With an alpha level of 0.05 and a power of 90%, each group will require 83 patients. However, it is necessary to state that the 5-year expected mortality rate (average age of 84 years) for the study group is approximately 60%. Therefore, the required number has increased by 2.5 times, and each study group requires a total of 200 patients. An interim analysis of the mortality identified this to be only 41% in our selected patient group and accordingly the sample size is reduced to 140 patients per group.

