### Randomization and blinding

2.2

An author will provide a set of 280 random numbers for the allocation sequence using a website (http://www.randomization.com). The random allocation sequence will be available to this author only and thus it will be concealed from the other research team members. The included participants will be randomly assigned to either the THA group or the HA group in a ratio of 1:1. The surgeons, anesthesiologists, and nurses providing intra- and postoperative care, as well as the research coordinator assessing outcomes, are all kept blinded to allocation results.

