### Statistical analysis

2.7

All data will be entered into STATA software (StataCorp; Texas, USA) by 3 investigators for statistical analysis and calculation. The accuracy of these data is analyzed by 2 other researchers. According to its distribution, the Mann–Whitney *U* test or Student *t* test is used to test the statistically significant differences between the treatment groups of HHS and other continuous parameters. Chi-square test or Fisher exact test is used to analyze dichotomous variables, such as revision and dislocation rates. All analyses are 2-sided analyses, and a *P* value of <.05 is considered statistically significant.

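### The sample-size chain (83, 200, 140 per group) does not follow from its own inputs and allows for no loss except death, so the 90% power needs to be qualified

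*Protocol article*

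**What the plan says.** All the sizing is in section 2.6 of the protocol article (Sample size calculation). It starts from the Harris hip score (HHS): "The smallest difference in HHS considered to be clinically important is 10 points", and "the maximum standard deviation is estimated to be 20 points". From these, "With an alpha level of 0.05 and a power of 90%, each group will require 83 patients".

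The section then cites an expected 5-year mortality of about 60% and scales up: "the required number has increased by 2.5 times, and each study group requires a total of 200 patients". Finally it reports that an interim look found mortality of 41%, and "accordingly the sample size is reduced to 140 patients per group". Section 2.2 matches this with 280 random numbers, and patients are "randomly assigned to either the THA group or the HA group in a ratio of 1:1".

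Section 2.7 fixes the sidedness, "All analyses are 2-sided analyses", and says that for HHS "the Mann–Whitney *U* test or Student *t* test is used", according to distribution. Section 2.5 places the last scheduled evaluation at 3 years. Death is the only form of attrition that the sizing mentions.

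**The concern.** Each figure in section 2.6 is presented as following from the one before, and each is slightly smaller than the arithmetic gives. Taken alone the gaps are small. Together they mean that the final size has nothing spare when the one attrition source it does not count appears.

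That source is a surviving patient without a final HHS: someone who withdraws, cannot attend or cannot be scored. Eligible patients are at least 80, and the section gives an average age of 84. Assuming that every survivor of such a cohort is scored at the last visit is a strong assumption, and the article does not state it.

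The abstract and the discussion both describe the trial as adequately powered for the primary outcome. That claim rests on this section, so the conditions under which it holds should be visible there.

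**Working it through.** **Inputs.** Difference 10, SD 20, alpha 0.05, power 90%, 60% and 41% mortality, multiplier 2.5, and 83, 200 and 140 per group: section 2.6. Two-sided tests: section 2.7. Allocation 1:1 and 280 in total: section 2.2. Last visit at 3 years: section 2.5. The loss rates among survivors in step 4 and the 3-year survival figures in step 5 are assumptions; the article gives none.

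**1. Evaluable patients per group.** Normal formula: n = 2 x (z for alpha/2 + z for power)² x (SD/difference)² = 2 x (1.960 + 1.2816)² x (20/10)² = 84.06, so 85. The noncentral t solution is 85.03, so 86. A one-sided test would give 69 (normal formula), so sidedness does not explain 83. Power at 83 per group is 89.6% (normal) or 89.3% (t). The plan's figure is thus reproduced to within two or three patients.

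**2. The step to 200.** 83 x 2.5 = 207.5, and 83/(1 - 0.60) gives the same. Read backwards, 200 x 0.40 = 80 survivors, which is below the plan's own 83 (t-test power 88.2%).

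**3. The step to 140.** 83/(1 - 0.41) = 83/0.59 = 140.7, so 141. The plan's 140 leaves 140 x 0.59 = 82.6 survivors, or 82 to 83. Power at 82.6 is 89.5% (normal) or 89.1% (t). Starting from 85 or 86 evaluable, the same step gives 145 or 146 per group.

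**4. Loss other than death**, at 140 per group and 41% mortality (two-sided t test):

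| Assumed loss among survivors | Evaluable per group | Power |
|---|---|---|
| 0% | 82.6 | 89.1% |
| 5% | 78.5 | 87.5% |
| 10% | 74.3 | 85.7% |
| 20% | 66.1 | 81.4% |

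**5. If 41% overstates deaths at the final visit.** To have 86 evaluable out of 140, the evaluable fraction must be 86/140 = 61.4%, so deaths and other losses together may not exceed about 38.6%. Two illustrations:

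- *41% is a 5-year figure and the hazard is constant.* Three-year survival is 0.59^(3/5) = 0.73, about 102 survivors per group. Power is 94.5% with no other loss and 92.1% with 10% loss among survivors.
- *Mortality at 3 years is 35%.* There are 140 x 0.65 = 91 survivors. Power is 91.8% with no other loss, 90.5% with 5% and 88.9% with 10%.

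**The case against.** The strongest reply is that most of this is rounding. A gap of two or three patients at 83, and of 0.4 patient at 82.6, costs about one point of power. The SD of 20 is called a maximum. By the normal formula, an SD of about 19.9 gives 83, and at 82.6 evaluable the t test reaches 90% with an SD of about 19.7. The 200 was superseded: the 140 follows from 83/0.59, so no current design figure depends on it. All of this stands.

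The second reply is that the size of any non-death loss is unknown, and that an offset may exist. Section 2.6 speaks of 5-year mortality, while section 2.5 ends follow-up at 3 years. If the 41% is a 5-year figure and HHS is analysed at 3 years, deaths are over-counted and the surplus could absorb other losses. This stands as a possibility. However, the article does not say what period the 41% covers and does not claim the difference as a reserve, so it cannot be credited to the stated 90% as the text now reads.

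A reader might go further and infer that the trial is underpowered, or that 90% should be replaced by one fixed lower figure such as 86%. The article supports neither. The shortfall on its own inputs is about one point, the 86% depends on an assumed 10% loss, and the mortality at the final visit is not settled. A separate calculation for the Mann–Whitney test is not warranted either. The usual efficiency figure of 0.955 applies to normal data, where a choice made by distribution would be expected to give the t test.

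**Conclusion.** The point holds in a limited form. The figures in section 2.6 do not chain: 85 or 86 is required and not 83, and 83 x 2.5 is 207.5 and not 200. The first error costs about one point of power, and the second has no effect on the final size. The defect of substance is that the inflation is for death only. At 41% mortality, 140 per group gives about 89% power if every survivor is scored, and any other missing HHS lowers it further, to between about 87.5% and 81% for assumed losses of 5% to 20%.

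These figures rest on SD 20, a 10-point difference, the t test, and 41% mortality at the time HHS is analysed. The last is uncertain: if deaths and other losses together stay at or below about 38.6%, 90% is reached. An unqualified 90% is therefore wrong as written, but the design is not shown to be inadequate.

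**What to change.** In section 2.6:

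1. Correct 83 to 85 (normal formula) or 86 (t test), naming the method.
2. Correct the 200 or delete it.
3. State the period that the 41% mortality covers, and reconcile the 5-year allowance with the 3-year final visit in section 2.5.
4. State that 140 per group at 41% mortality yields about 82 to 83 evaluable patients and about 89% power before non-death loss. Add a range for assumed non-death loss (for example 5% to 20% among survivors), in place of the unqualified 90%.
5. If mortality at the 3-year visit is expected to be below 41%, say so, and give the resulting power, which may reach or exceed 90%.

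The cost is a revision of text. Enrolment stays at 140 per group if the restated power is accepted; the stated power becomes conditional and, at 41% mortality, slightly lower.

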### Outcome measurements

2.5

Patients will be evaluated at 3 months, 6 months, 1 year, and 3 years after surgery. At the time of the final follow-up, patients were assessed with use of the Harris hip score (HHS) and walking distance. The walking distance at the time of the final follow-up is reported by the patients themselves. Anteroposterior and lateral radiographs of the involved hip are made. Secondary outcomes of interest include postoperative complications, including 90-day medical complications (acute myocardial infarction, deep vein thrombosis, pulmonary embolism, intestinal obstruction, renal failure, and pneumonia) and surgical complications within 1 year (dislocation, infection, and revision replacement).

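### The sample size is inflated for 5-year mortality, but the Harris hip score is read at a final follow-up of 3 years, so 140 per group and 90% power are not derived for this endpoint

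*Protocol article*

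**What the plan says.** The Sample size calculation section (2.6) states the target first: "The smallest difference in HHS considered to be clinically important is 10 points", "the maximum standard deviation is estimated to be 20 points", and "With an alpha level of 0.05 and a power of 90%, each group will require 83 patients". It then allows for deaths, on the ground that "the 5-year expected mortality rate (average age of 84 years) for the study group is approximately 60" per cent. This raises the number 2.5-fold, to 200 per group. Finally it cuts that figure to 140 per group: "An interim analysis of the mortality identified this to be only 41% in our selected patient group and accordingly the sample size is reduced".

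The Outcome measurements section (2.5) gives the schedule: "Patients will be evaluated at 3 months, 6 months, 1 year, and 3 years after surgery". HHS and walking distance are taken at the final follow-up, and the Abstract says the same. The article schedules no visit later than 3 years.

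The Randomization and blinding section (2.2) matches the reduced size: "An author will provide a set of 280 random numbers for the allocation sequence", which is 2 × 140. The Abstract and the Discussion both describe the trial as powered for its primary outcome.

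**The concern.** Inflation for death should use the share of patients expected to be dead when the outcome is measured. Here the share is a 5-year figure and the outcome is read at 3 years.

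The figure that fixes the final size adds a second difficulty. By grammar the 41% replaces the 5-year rate, but a trial whose last visit is at 3 years does not yield an observed 5-year rate. The 41% may have been seen at some earlier follow-up, or in another set of patients; the text does not say.

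This matters because the 41% alone takes 60 patients per group out of the plan. If it was measured earlier than 5 years, part or all of the apparent gain over 60% could come from comparing two different time points. The statement that the trial is powered for HHS rests on this one number.

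**Working it through.** **Inputs.** From section 2.6: difference 10, SD 20, alpha 0.05, power 90%, 83 evaluable per group, mortality 60% at 5 years, then 41%, final size 140 per group. From section 2.7: two-sided tests. From section 2.5: last visit at 3 years. Assumed, because the article does not give it: a constant death hazard, used only to move between time points. Death is the only loss counted, as in the article.

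**The plan's own figures.**
- Evaluable number: 2 × (1.960 + 1.282)² × (20/10)² = 84.06, so 85 per group against 83 stated. This is close enough.
- First inflation: 83/(1 − 0.60) = 207.5 against 200 stated. This is slightly off, but superseded.
- Final inflation: 83/(1 − 0.41) = 140.7, so 141 against 140 stated. This agrees.

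The arithmetic is sound. The stated power therefore applies if about 41% have died when HHS is measured: 140 × 0.59 = 82.6 evaluable per group.

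**Moving to 3 years.** If a proportion d has died by year t, 3-year survival is (1 − d)^(3/t), and the evaluable number is m = 140 × survival. Power is that of a two-sided t test with standardised difference 10/20 = 0.5. It is close to Φ(0.5 × √(m/2) − 1.96). The last column is 84.06 divided by 3-year survival, rounded up.

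| Meaning of the mortality figure | 3-year survival | 3-year mortality | Evaluable of 140 | Power at 3 years | Per group for 90% |
|---|---|---|---|---|---|
| 41% at 5 years | 0.59^(3/5) = 0.729 | 27% | 102 | about 94% | 116 |
| 41% at 3 years | 0.590 | 41% | 83 | about 89% | 143 |
| 60% at 5 years, as first planned | 0.40^(3/5) = 0.577 | 42% | 81 | about 88% | 146 |
| 41% by 2 years | 0.59^(3/2) = 0.453 | 55% | 63 | about 80% | 186 |

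**What the table shows.** The planned 60% at 5 years already implies about 42% at 3 years. If the 41% was seen at about 3 years, survival is no better than planned. The cut from 200 to 140 would then reflect a change of horizon, not fewer deaths. At a 3-year endpoint 140 per group would still give nearly the intended power.

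**The case against.** The strongest reply is that no harm is shown at the documented endpoint. Read plainly, the 41% is a 5-year rate. Mortality at 3 years cannot exceed mortality at 5 years, so at least 82.6 per group remain and power is at least about 89%, with no hazard assumption. On that reading the mismatch is conservative. Even the first-planned 60% leaves about 88% at 3 years. Power falls clearly below 90% only if 41% had died before year 3, and nothing in the article says so. All of this stands, and it limits the point to an unsupported power figure.

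A reader might go further and infer power of only 75% or 76%. The article does not support that. The 75% needs 60% dead at the HHS assessment (140 × 0.40 = 56 evaluable); at 3 years, that would put all the deaths expected over five years into the first three. The 76% needs 41% at 3 years and an endpoint at 5 years (140 × 0.59^(5/3) = 58 evaluable), but no 5-year visit exists.

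A reader might also infer that the interim look came before randomisation, because the allocation list is still to be produced. That rests on verb tense, and section 2.5 itself mixes future and past. The group that gave the 41% may be an earlier cohort. Whether the look was pooled over arms is detail that a condensed article may leave to the full protocol.

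The format does not explain the rest. The 5-year horizon, the 3-year schedule and the size built on the first of these are all stated, and they do not fit together.

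**Conclusion.** The point holds as an inconsistency between sections 2.5 and 2.6. The final size and the 90% power are derived from mortality at a horizon the trial does not reach, using a 41% with no follow-up time of its own. An observed 5-year rate cannot come from patients followed on this schedule.

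The 90% is unsupported for this design; it is not shown to be too high. At 3 years, with 140 per group and the article's difference and SD, power runs from about 80% to about 94%, depending on when the 41% applies. The readings closest to the text give 88% to 94%. The 80% depends on a 2-year time point that is purely an assumption. The 3-year conversions rest on a constant hazard, except where the 41% is itself taken as 3-year mortality. None allows for loss other than death. This should be fixed, but it does not invalidate the trial.

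**What to change.** 1. Put sections 2.5 and 2.6 on one horizon. If HHS is read at 3 years, base the inflation on expected 3-year mortality and give its source.
2. State in which patients and at what length of follow-up the 41% was observed. If it comes from an earlier cohort, call it a planning estimate and not an interim analysis.
3. Redo the inflation with mortality at the HHS visit. Restate the evaluable number and the power for 140 per group. Until the 41% is dated, give the 3-year range of about 80% to 94% with its assumptions.
4. Quote figures of 75% to 76% only if the endpoint is moved to 5 years, in which case section 2.5 needs a matching visit.

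The cost is a few sentences and possibly a slightly less favourable power statement. The rewrite requires no extra patients.

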### Statistical analysis

2.7

All data will be entered into STATA software (StataCorp; Texas, USA) by 3 investigators for statistical analysis and calculation. The accuracy of these data is analyzed by 2 other researchers. According to its distribution, the Mann–Whitney *U* test or Student *t* test is used to test the statistically significant differences between the treatment groups of HHS and other continuous parameters. Chi-square test or Fisher exact test is used to analyze dichotomous variables, such as revision and dislocation rates. All analyses are 2-sided analyses, and a *P* value of <.05 is considered statistically significant.

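### Deaths enter the plan only as lost sample size: HHS is compared among survivors, and mortality is not a named outcome

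*Protocol article*

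**What the plan says.** In the protocol article, Outcome measurements schedules visits at 3 months, 6 months, 1 year and 3 years and has HHS and walking distance assessed at the final follow-up. Under Statistical analysis, a Mann–Whitney or Student t test, chosen by distribution, "is used to test the statistically significant differences between the treatment groups of HHS and other continuous parameters". No analysis population is given there, and no rule for patients who die.

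Death appears under Sample size calculation. The target is stated as "With an alpha level of 0.05 and a power of 90%, each group will require 83 patients". That number was first raised 2.5-fold to 200 per group for an expected 5-year mortality of about 60%. An interim analysis then "identified this to be only 41% in our selected patient group", and the size was cut to 140 per group.

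The outcome lists do not contain death. "Secondary outcomes of interest include postoperative complications, including 90-day medical complications" introduces six medical events, followed by three surgical events within 1 year. The Abstract gives the same list. The Discussion nevertheless counts keeping mortality low among the aims of treating these fractures.

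**The concern.** Enrolling more patients to offset deaths restores the power of the HHS test. It does not restore the randomised comparison. Patients alive at the final visit are selected after randomisation. If one operation leads to more deaths, or to deaths in a different kind of patient, the survivors in the two arms are no longer alike at baseline. An arm that lost more frail patients could then show a higher mean HHS with no functional benefit from the operation.

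The protocol's Introduction describes hemiarthroplasty as the simpler procedure with less blood loss, so a mortality difference cannot be ruled out in advance. Without mortality compared by arm, a reader of the results could not tell whether the survivor comparison is sound, and a difference in deaths could go unreported beside a functional result.

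**Working it through.** **Inputs from the protocol article.** Important difference 10 points ("The smallest difference in HHS considered to be clinically important is 10 points"); standard deviation 20 ("the maximum standard deviation is estimated to be 20 points"); alpha 0.05 two-sided ("All analyses are 2-sided analyses, and a *P* value of <.05 is considered statistically significant"); power 90%; 1:1 allocation ("randomly assigned to either the THA group or the HA group in a ratio of 1:1"); mortality 41%; 140 per group.

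**Step 1: the plan's evaluable number.** n = 2 × (1.960 + 1.282)² × (20/10)² = 84.06, so 85 per group. An exact t-test calculation gives 85.03. The stated 83 is within two patients of this.

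**Step 2: the inflation for deaths.** 83 / (1 − 0.41) = 140.7, against the stated 140. In reverse, 140 × 0.59 = 82.6 survivors and 140 × 0.41 = 57.4 deaths per group. Over both groups that is about 165 of 280 patients in the HHS test and 115 outside it. Power among 82.6 survivors per group is 89.5% (normal approximation) or 89.1% (t test). The sample size therefore works as intended, and what it provides for is a comparison of survivors.

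**Step 3: how firm is the 41%?** It replaces a 5-year rate, while the last scheduled visit is at 3 years, and the text does not say which time it refers to. If it is a 5-year figure and the hazard is constant (an assumption), mortality at 3 years is 1 − 0.59^(3/5) = 27.1%, or 38 of 140 per group. The loss from the HHS comparison is thus about 38 to 57 per group, depending on the reading.

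**Step 4: possible size of the bias (illustration; none of these inputs is in the protocol).** Suppose there is no true HHS effect, the standard deviation is 20, and each patient has a latent survival score with correlation ρ to HHS. Patients below the cut-off c = Φ⁻¹(p) die, where p is the mortality in that arm. Mean HHS among survivors is then raised by 20ρ × φ(c)/(1 − p).

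- p = 0.36: c = −0.358, φ(c) = 0.3741, ratio 0.3741/0.64 = 0.5846.
- p = 0.46: c = −0.100, φ(c) = 0.3969, ratio 0.3969/0.54 = 0.7351.
- Difference in ratios 0.1505, so the bias is 20 × 0.1505 × ρ = 3.01ρ.
- Survivors: 140 × 0.64 = 89.6 and 140 × 0.54 = 75.6. Standard error 20 × √(1/89.6 + 1/75.6) = 3.12.

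Type I error = 1 − Φ(1.96 − bias/SE) + Φ(−1.96 − bias/SE).

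| Mortality by arm | ρ | Spurious difference (points) | Type I error |
|---|---|---|---|
| 41% v 41% | 0.3 or 0.5 | 0 | 5.0% |
| 36% v 46% | 0.3 | 0.9 | 6.0% |
| 36% v 46% | 0.5 | 1.5 | 7.7% |
| 36% v 46% | 0.7 | 2.1 | 10.4% |
| 31% v 51% | 0.3 | 1.8 | 8.9% |
| 31% v 51% | 0.5 | 3.0 | 16% |

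In each case the spurious gain goes to the arm with more deaths.

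**Step 5: would a mortality comparison detect this?** For 36% v 46% with 140 per arm, z = 0.10 / √[(0.36 × 0.64 + 0.46 × 0.54)/140] = 1.71, and power is Φ(1.71 − 1.96), about 40%. For 31% v 51% it is about 93%.

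**The case against.** The strongest defence is that the article condenses a fuller document. Analysis sets, missing-data rules and supporting analyses are commonly left to the full protocol or the SAP, and the text never says in words that only survivors are compared. That is fair as far as wording goes. But the article builds its final sample size on exactly that comparison (step 2), and it lists its outcomes explicitly. The verb introducing the secondary outcomes may leave the list open, but death is named as an outcome nowhere.

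Several stronger readings are tempting and are not supported:

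- **That the HHS result will be biased.** Nothing in the protocol gives a mortality difference between arms. The splits and correlations in step 4 are assumed, and with equal mortality and equal selection the bias is zero. Even the largest illustrated value, 3.0 points, is well short of the 10-point important difference.
- **That 41% will be dead at the HHS assessment.** The plan uses 41% as its loss, but the time point is unclear, and about 27% is possible on a constant hazard. This lowers the number without removing the problem.
- **That an arm with more early deaths would show fewer 90-day complications.** The documents give no rates to size this, and several listed events (myocardial infarction, pulmonary embolism, renal failure, pneumonia) may precede a death and would then be counted.
- **That a functional conclusion should be allowed only when the HHS and mortality results agree.** Such a rule needs a criterion for disagreement. At about 40% power for 36% v 46%, a mortality test would often miss the imbalance in question.

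**Conclusion.** The point holds as a weakness in the planned analysis and outcome list. The plan answers death only with a larger sample, compares HHS in a post-randomisation subset expected to be about 83 of 140 per arm (about 102 of 140 if the 41% is a 5-year figure and the hazard is constant), and does not name mortality for comparison by arm.

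That the comparison is restricted to survivors follows from the plan's own arithmetic. The amount of bias is uncertain: 0.9 to 2.1 points and a type I error of 6.0% to 10.4% for mortality of 36% v 46% and a correlation of 0.3 to 0.7, and none with equal mortality and selection. The case for change is that results reported under this plan would not let a reader judge which situation applies. The change is worth making, but the trial does not depend on it.

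**What to change.** 1. Add all-cause mortality by arm at 90 days, 1 year and 3 years to the secondary outcomes.
2. Keep the planned HHS test, and state that it estimates a difference conditional on being alive at the final follow-up.
3. Report beside it a supporting Mann–Whitney analysis of all randomised patients, with deaths ranked below every survivor.
4. State the time point to which the 41% refers.

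Reporting death or complication at 90 days as a combined outcome is optional.

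**Cost.** Neither the sample size nor clinical care changes. Vital status by arm is needed at the three time points; the interim analysis shows that mortality is already being followed. The rank analysis mixes death with function and has less power for a pure HHS effect. The mortality comparison has limited power (about 40% for 36% v 46%). Both should therefore be labelled as supporting analyses, and a non-significant mortality result should not be read as showing that the arms are equal.

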### Eligibility criteria

2.3

Inclusion criteria include: displaced intracapsular femoral neck fracture, capability to obtain informed consent, no known metastatic disease, no contraindications to anesthesia, age ≥80 years, and ability to understand written Chinese. The exclusion criteria are: failure to meet the inclusion criteria, including refusal of consent, radioactive osteoarthritis of hip fracture or rheumatoid arthritis; suspected pathological fractures; patients who are bedridden or could barely move to a chair; Alzheimer disease.

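### The HHS comparison is fixed as an unadjusted two-sample test although age is known for every patient at entry; a prespecified age- and sex-adjusted model would be more efficient at little cost

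*Protocol article*

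**What the plan says.** All references are to the protocol article.

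- **Section 2.7 (Statistical analysis):** a Mann–Whitney U or Student t test, picked according to the distribution, "is used to test the statistically significant differences between the treatment groups of HHS and other continuous parameters". No regression model, covariate or stratified analysis is named. On sidedness: "All analyses are 2-sided analyses".
- **Section 2.2 (Randomization and blinding):** patients are "randomly assigned to either the THA group or the HA group in a ratio of 1:1". No stratification factor is named.
- **Section 2.3 (Eligibility criteria):** a minimum age of 80 is an entry criterion, so age is established for each patient before randomisation. Mobility appears only as an exclusion: "patients who are bedridden or could barely move to a chair".
- **Section 2.5 (Outcome measurements):** HHS is assessed at the final follow-up, so only patients alive then can contribute.
- **Section 2.6 (Sample size calculation):** the requirement for an unadjusted comparison is given first here: "With an alpha level of 0.05 and a power of 90%, each group will require 83 patients". The target difference behind it is set out separately: "The smallest difference in HHS considered to be clinically important is 10 points". The SD is taken as 20 points, described as a maximum. On deaths the section adds: "An interim analysis of the mortality identified this to be only 41% in our selected patient group", and the planned number then becomes 140 per group.

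**The concern.** Neither the allocation nor the analysis, as written, makes use of a prognostic baseline variable. A linear model with prespecified baseline covariates estimates the same mean difference that the sample size calculation targets. It has a smaller standard error to the extent that the covariates predict HHS.

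Two features of this trial make that worth considering. First, HHS comes only from survivors. Randomisation balances the 140 per group who enter, but it does not guarantee balance among those who reach the final visit, and a raw comparison leaves any age difference between the surviving groups in the estimate. Second, on the plan's own inputs the expected number of survivors sits almost exactly at the stated requirement, so a modest gain in precision falls where the calculation has little room.

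At stake are the width of the confidence interval and a few points of power. The validity of the test is not in question.

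**Working it through.** **Inputs from the article.** Difference 10 HHS points, SD 20 (stated as a maximum), two-sided alpha 0.05, power 90%, stated requirement 83 per group, mortality 41%, 140 randomised per group.

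**Assumptions.** R², the share of HHS variance explained by the covariates, is not in the article; a range of 0 to 0.20 is used. The 41% mortality is taken to apply at the final visit.

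**1. The plan's own figures.**
- Normal approximation: n = 2 × [20 × (1.960 + 1.282) / 10]² = 84.06, rounded up to 85 per group. The t-based figure is 85.03. The stated 83 is within 2 patients.
- Inflation for 41% deaths: 83 / 0.59 = 140.7, so 141 against the stated 140.

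The plan's numbers therefore reproduce closely for an unadjusted test.

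**2. Unadjusted power among survivors.** 140 × 0.59 = 82.6 per group. With 82 whole patients per group, a two-sample t test (noncentral t) has power 88.9%. With 82.6 it is 89.1%, or 89.5% by the normal approximation.

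**3. Adjusted analysis, 82 per group.** Residual SD = 20 × √(1 − R²). Equivalent unadjusted n = 82 / (1 − R²).

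| Assumed R² | Residual SD | Power | Equivalent unadjusted n per group |
|---|---|---|---|
| 0 | 20.00 | 88.9% | 82 |
| 0.01 | 19.90 | 89.2% | 82.8 |
| 0.05 | 19.49 | 90.4% | 86.3 |
| 0.10 | 18.97 | 91.8% | 91.1 |
| 0.20 | 17.89 | 94.5% | 102.5 |

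**4. What adjustment costs.** The degrees of freedom used by the covariates cost under 0.01 percentage points of power. Chance covariate imbalance also inflates the variance of the treatment estimate on average, by about 1 + k/(N − k − 3) for normally distributed covariates. With k = 2 covariates and N = 164 this is 1 + 2/159 = 1.0126. Allowing for it, power is 88.5% at R² 0, 88.9% at 0.01, 90.0% at 0.05, 91.5% at 0.10 and 94.2% at 0.20. The model breaks even at R² = 1 − 1/1.0126 = 0.012.

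**5. Effect of imbalance on the estimate.** With 82.6 per group, the chance difference in a standardised covariate has SE √(2/82.6) = 0.156. An imbalance of d standard deviations in a covariate with correlation R to HHS moves the raw HHS difference by R × 20 × d. For a 2-SE imbalance (d = 0.31) the shift is 0.6 points at R = 0.1, 1.9 at R = 0.3 and 3.1 at R = 0.5, against a target of 10.

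**The case against.** Several points on the other side have force.

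- **The test is valid.** A reader might infer that the plan contains an error. It does not: under randomisation the unadjusted test is legitimate, and it is the test for which the sample size was calculated. This stands, and it is why the point concerns efficiency only.
- **Mobility is not available as a covariate.** A reader might infer from the exclusion criterion that a mobility level is already on file. The article describes only a yes/no screen that every enrolled patient has passed, so as documented it does not vary. A graded level would have to be added. This stands.
- **The gain may be small.** The article gives no correlation with HHS, and age limited to 80 and over may explain little. At R² 0.01 the gain is 0.3 points before the average cost of fitting two covariates and nil after it. This stands.
- **Power may not be tight.** SD 20 is a stated maximum; at SD 18, 82 per group give about 94% unadjusted. The 41% also replaces a 5-year mortality figure, whereas the last listed visit is at 3 years, so more patients may be alive then. A reader should not conclude that the trial is underpowered for want of adjustment.
- **Survivor selection remains.** Regression handles measured covariates only. It cannot undo differential death related to unmeasured frailty.
- **An unseen analysis plan might adjust.** That is possible, but section 2.7 does not leave the method open: it names the test. Replacing a named test is different from asking for omitted detail.

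These objections limit the size and wording of the point. None makes the unadjusted test preferable as the primary analysis.

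**Conclusion.** The point holds as an efficiency improvement. The HHS test is fixed without covariates although age is known at entry and no stratification factor is named. On the assumptions of 82 survivors per group and SD 20, power moves from 88.9% to between 89.2% (R² 0.01) and 94.5% (R² 0.20), or between 88.9% and 94.2% once the average cost of two covariates is counted. If the covariates explain nothing, the loss is about 0.4 percentage points. The range is an assumption, since the article offers nothing from which to estimate R². Adjustment would also reduce the effect of measured age or sex imbalance among survivors. The documents do not support going further, to an invalid analysis, an underpowered trial or a cure for selection through death.

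**What to change.** In section 2.7, name the primary HHS analysis as a prespecified linear regression of HHS on treatment group, age (continuous) and sex, with robust standard errors, reporting the adjusted mean difference and its 95% CI. Keep the unadjusted test as a sensitivity analysis. A single model also removes the data-dependent choice between a test of means and a rank test, and it estimates the mean difference that section 2.6 powers.

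Optionally, record a graded pre-fracture mobility level at entry and add it to the model.

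The cost is one sentence in the plan, with no extra patients or visits. Age is already needed for eligibility. Sex is not mentioned in the article but is routinely recorded. The mobility option needs one additional baseline item.
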